#### Screening procedure

Inclusion criteria will be assessed over the telephone or in-person by [name], the research coordinator, or trained undergraduate research assistants. All screening personnel will undergo training prior to data collection to ensure all screening will be administered according to standardized instructions. There is no special expertise required to make inclusion/exclusion decisions. At first contact with potential participants, screening personnel will provide a description of the study using a telephone script. Potential participants will then be screened for age, diagnosis of MS, relapse status, willingness to visit Berry College on 27 occasions, disability status, asymptomatic status, and ability to speak, read, and understand English. Potential participants who meet these criteria will be sent forms for documenting the confirmed diagnosis of MS and obtaining medical clearance for exercise testing. Final decisions regarding participant inclusion will be made only once all screening materials have been received and reviewed. [name] will make final decisions on participant inclusions/exclusion. We will retain screening data for those who qualify and volunteer to participate and destroy screening data from those who do not qualify or do not volunteer.

#### MS verification and medical clearance procedure

Screened individuals who qualify for the study will be sent an information packet via email or through the US postal service. This packet will include the Informed Consent document, MS Verification form, and Physician’s Approval form. Participants may give verbal approval for study investigators to send MS Verification and Physician’s approval forms to the neurologist or physician directly via fax or confidential email. All forms need to be signed and returned by email, fax, regular mail, or in person before the participant is officially enrolled.

#### Process log

A process log will be maintained on a password-protected database to assess enrollment patterns and study feasibility. The log will contain the following demographic information: identification number, individuals’ name, and contact information. The log will also be used to track screening date, eligibility status, date enrolled, reason for ineligibility, reason for refused consent/participation, adherence, and source of subject (e.g., referral, advertising, advocacy, etc.). We will record adherence with the intervention via log books to be filled out at each completed or missed exercise session.

#### Retention plan

To promote adherence, participants will receive email-based newsletters intermittently throughout the program. These newsletters will include topics related to Social Cognitive Theory-based behavior change techniques, such as outcome expectations, self-monitoring, goal-setting, self-efficacy, and barriers and facilitators [28]. The newsletters will include instructions on behavioral techniques to improve intervention compliance and websites for more information on each of the topics included [28]. In addition to the newsletters, testing and training sessions will be scheduled based on the participant’s schedule and preferred times in order to encourage adherence and retention. Reminders will be sent via email or phone 24 h before each session. These reminders will be sent as emails or calls, based on participant preference. Participants will be also allowed to reschedule makeup sessions within each week if a regularly scheduled session is canceled. After midpoint testing, training will be adjusted based on testing outcomes to ensure all participants continue to receive appropriate treatment.

### Feasibility metrics

We adopted a feasibility study design aimed at providing experience and preliminary data for advancing to a proof-of-concept study in a RCT [32]. Process, resource, management, and science feasibility outcomes will be used to determine how the study is conducted in addition to identifying any perils or pitfalls that could lead to traps and stumbling blocks in a proof-of-concept RCT [32]. Thus, a single treatment group, repeated measures study design is proposed. No control group will be used because we specifically aim to identify the feasibility and preliminary efficacy of the HIIT exercise protocol alone in pwMS-wd [38].

Process, resource, management, and scientific metrics will be measured throughout the entirety of the research study [28, 32]. Table 1 presents the four different feasibility metrics, the specific outcomes related to each metric, how these outcomes will be monitored and assessed, and how the specific metrics are relevant to future phase II and III studies. In brief, the process feasibility outcomes assess participant recruitment and retention, which will provide optimal recruitment methods, expected recruitment rates, and refusal reasons. The resource feasibility outcomes will evaluate any research-stage-dependent time and resource issues that can occur and provide expected retention rates, barriers to participation, compliance rates, participant experience of the program and outcome assessments, suitability of the proposed setting, staff training needs, and monetary costs to conduct the research and establish areas for cost saving. The management feasibility outcomes identify potential human and data management issues and will provide detailed staff time requirements, highlight considerations for alterations, and detail recommended safety procedures. Scientific feasibility outcomes will examine the safety, burden, and treatment effect of the study. Participants’ experience, burden, and perceptions of intervention appropriateness will be assessed, and the treatment effect will be determined through calculating effect sizes for all of the clinically relevant efficacy outcomes. Effect sizes will also be used for power calculations for a proof-of-concept RCT [28, 32].

**Table 1 Tab1:** Feasibility metrics, proposed methodology, and importance to future research in multiple sclerosis

Metric	Specific outcomes	Outcome assessment	Importance to future phase II and III studies
**Process** (i.e., participant recruitment, retention, and adherence assessment)	1. Recruitment and refusal rates 2. Retention and attrition rates 3. Adherence rates to study procedures, intervention attendance, and engagement	1. Flyers and presentations at local and regional support group chapters, National Multiple Sclerosis Society events, clinics and doctor’s offices, advertisements on social media, email communication, and word of mouth will be used to recruit potential participants. All contact methods with potential participants and refusal reasons will be recorded. 2. The flow of participants through the recruitment, enrollment, and intervention stages of the study will be recorded. 3. Adherence rates will be recorded via individual log books.	1. Provides information for optimizing recruitment methods, anticipated recruitment numbers, and refusal reasons. 2. Specifies focal areas for enhancing participant retention. 3. Provides target areas for optimizing adherence to the intervention.
**Resource** (i.e., time and monetary needs assessment)	1. Staff training requirements 2. Communication time and content requirements and alterations 3. Recruitment and intervention time requirements 4. Monetary research costs	1. Staff training needs will be recorded. 2. A password-protected database will be used to monitor all contact between participants and staff members. Communication type, purpose, and any alterations will be recorded 3. Detailed staff time requirements for recruitment, testing, and training will be recorded. Individual log books will be used to record individual testing and training requirements for each participant. 4. All study-related monetary costs will be recorded.	1. Details staff training requirements. 2. Establishes communication frequency and quality and emphasizes communication problems. Details communication needs and anticipated communication problems. 3. Details staff and participant time requirements for delivering and engaging in the intervention, respectively. 4. Determines monetary cost to conduct the research and establishes areas for cost saving.
**Management** (i.e., data management and safety reporting assessment)	1. IRB approval procedures 2. Time and accuracy in data collection, entry, and checking	1. All Institutional Review Board (IRB) approval procedures will be documented and will include communications between the University IRB and staff, and time from submission of IRB application to approval. 2. Data will be checked for completeness and errors. All time spent collecting, entering, and checking data will be recorded.	1. Details procedural and staff requirements for obtaining ethical approval, compliance, and monitoring. Highlights optimal safety procedures to be implemented. 2. Identifies staff time requirements and highlights considerations for alterations to ensure proper data management.
**Scientific** (i.e., safety, burden, and treatment effect assessment)	1. Adverse events, serious adverse events, and clinical emergencies 2. Participants’ experience, burden, and perceptions 3. Treatment effect	1. Adverse events, serious adverse events, and clinical emergencies will be reported and recorded. A safety plan will be enacted in the occurrence of an adverse event wherein participants will be asked to discontinue the HIIT exercise and cool-down (if currently exercising) and will be required to be free of symptoms for at least 48 h before returning to activity. 2. Participants’ experience, burden, and perceptions of intervention appropriateness will be assessed via a short survey at the end of the intervention. 3. Treatment effects will be determined via effect size and clinical meaningfulness calculations of any change in the efficacy outcome variables.	1. Establishes the safety and feasibility of the intervention and identifies considerations for alterations. 2. Determines the acceptability and highlight considerations for alterations. Identifying compliance will further allow correct conclusions to be drawn from the results. 3. Establishes data for power calculations and projected clinical impact.

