### Screening, eligibility criteria, and retention

#### Inclusion criteria

Participants who meet the following criteria will be included: (a) age 18–64 years, (b) a self-reported diagnosis of MS, (c) self-reported Expanded Disability Status Scale (EDSS) score < 8.0 or Patient Determined Disability Steps (PDDS) scale score ≤ 7.0, (d) relapse free in past 30 days, (e) willing and able to visit Berry College on three testing occasions and twenty-four training occasions, (f) asymptomatic status for maximal exercise testing, (g) physician approval for undertaking exercise testing, and (h) a self-reported ability to speak, read, and understand English. Participants who do not meet those criteria will be excluded from study participation. Age, self-reported MS diagnosis, relapse status, and willingness to visit Berry College’s campus will be assessed using a simple checklist. Confirmed MS diagnosis will be based on a letter from the participant’s neurologist. Disability status will be determined using the self-reported EDSS and the PDDS scale. Asymptomatic status is defined as one or fewer affirmatives on the Physical Activity Readiness-Questionnaire (PAR-Q). MS verification and medical clearance for exercise testing will be provided by the participant’s physician.

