### Safety reporting

#### Risks

The risks to participants are considered to be low and no more than typical daily life. There is little serious risk associated with the completion of the incremental exercise test and exercise sessions. The completion of maximal exercise always involves risks of death, acute myocardial infarction (i.e., heart attack), and complications that require hospitalization. There are risks of slips, trips, and falls during the assessment of functional ability. There are potential risks of becoming frustrated when completing the cognitive assessments. This will be reduced by providing clear instructions and practice tests. We will fully inform participants of the risks associated with the cognitive measures in the informed consent document. Participants will be allowed to discontinue their participation in the study at any time.

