#### Protections against risk

All efforts will be made to protect against or minimize all potential identified risks. All participants will be informed of the risks associated with study participation in the informed consent document.

Risks associated with aerobic capacity outcomes and exercise training will be minimized by screening for individuals with factors placing them at increased risk for complications. All personnel will be trained in CPR and emergency lab procedures and will call 911 and [name] in the event of a serious adverse event as outlined in Berry College’s policies and procedures. Importantly, exhaustion, fatigue, and muscle soreness are associated with maximal aerobic exercise and strength testing, but are temporary symptoms. Participants will be encouraged to warm-up and/or stretch before any assessment of fitness or exercise session in order to minimize these symptoms. Participants will further wear clothing appropriate for exercise. Environmental regulation (e.g., use of a fan) will keep the participant cool during the sessions and avoid symptom exacerbation. Risks associated with motor function assessments will be minimized by allowing for the use of assistive devices (i.e., ankle-foot orthoses, canes, and walkers) during testing as well as having a gait belt around the participants’ waist and a research assistant within arm’s reach for stabilizing the participant in the event of a slip, trip, or fall. The testing will further be conducted in a hallway or close to a wall such that participants are able to stabilize themselves when necessary. Risks associated with the cognitive outcomes will be reduced by providing clear instructions and practice tests.

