#### Reporting of adverse or serious adverse events

Participants will be instructed to notify research staff immediately when an adverse or serious adverse event occurs. [name] will report the AE or SAE to the Berry College Institutional Review Board. This report will include information on the event type, event severity, event expectedness, study relatedness, description of the event, and any and all steps and actions taken in response to the incident or to resolve the issue.

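### The only stated condition for returning to exercise, at least 48 h without symptoms, has no higher level for a serious adverse event or clinical emergency.

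*Protocol article*

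**What the plan says.** The Scientific row of Table 1 lists three classes of event for recording: "Adverse events, serious adverse events, and clinical emergencies will be reported and recorded". The next sentence sets out one safety plan, triggered by an adverse event. The participant stops the interval exercise, cools down if exercising, and "will be required to be free of symptoms for at least 48 h before returning to activity".

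Physician approval is an entry requirement. Inclusion criteria lists "g) physician approval for undertaking exercise testing", and MS verification and medical clearance procedure adds: "All forms need to be signed and returned by email, fax, regular mail, or in person before the participant is officially enrolled". No later approval is mentioned.

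Under Safety reporting, Risks states: "The completion of maximal exercise always involves risks of death, acute myocardial infarction (i.e., heart attack), and complications that require hospitalization". Protections against risk says that the risks of fitness testing and training "will be minimized by screening for individuals with factors placing them at increased risk for complications", and that staff will call emergency services and a study contact "in the event of a serious adverse event", following college policy. Reporting of adverse or serious adverse events requires a report to the ethics board that includes "any and all steps and actions taken in response to the incident or to resolve the issue".

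**The concern.** The article separates three classes of event when it records them but states a single threshold for resuming exercise. In ordinary usage a serious adverse event is an adverse event, so the 48 h rule as worded covers it.

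The main protection against exercise risk is screening at entry. A serious event on study can change the risk that the physician assessed, and a symptom-free interval of two days does not show that maximal effort is acceptable again. Exposure continues after entry, with intervals at 90% of peak oxygen uptake for 12 weeks and further tests to volitional fatigue at T2 and T3. What is at stake is participant safety. The study is also meant to recommend safety procedures for the later randomised trial, so an ungraded rule could be carried into it.

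**Working it through.** The point is one of wording, so the check sets the relevant sections side by side and asks of each whether it states a condition for return after a serious event.

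| Section | What it governs | Condition for return after a serious event? |
|---|---|---|
| Table 1, Scientific row | Recording of all three classes; one safety plan | Only the 48 h minimum, not graded |
| Inclusion criteria | Physician approval and asymptomatic status | No; entry only |
| MS verification and medical clearance procedure | Signed forms | No; before enrolment only |
| Exercise intervention | Supervised sessions with safety monitoring | No |
| Protections against risk | Emergency call for a serious event | No; immediate response only |
| Reporting of adverse or serious adverse events | Report to the ethics board, including severity, relatedness and actions | No; return does not depend on the report |

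Three things follow.

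1. The immediate response and the reporting take account of seriousness. The return rule does not.
2. Entry requires a physician's signature. Return after a serious event, as stated, requires none. The stated bar for coming back is therefore lower than the bar for coming in.
3. Followed literally, the text lets a participant resume intervals, or take the T2 or T3 maximal test, on an approval signed before the event.

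The plan gives no figure to reproduce here. The only arithmetic concerns what a hold would cost in sessions. Go criterion 1 (Data analysis) needs 20 of 24 sessions, so 24 − 20 = 4 may be missed. Assume a hard stop at 12 weeks and no catch-up:

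- **Twice a week:** 4 / 2 = 2 weeks. Any hold of up to 14 days leaves at least 20 sessions; a 15-day hold can take 5 and leave 19.
- **Monday, Wednesday, Friday:** 12 × 3 = 36 possible sessions, so 36 − 20 = 16 may be missed. A hold of 37 days (5 weeks plus 2 days) takes at most 15 + 1 = 16 and leaves 20. A hold of 38 days can take 15 + 2 = 17 and leave 19.

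The no-catch-up assumption is severe. Retention plan allows make-up sessions within a week, and Exercise intervention lets participants change their frequency. For example, a three-week hold at two sessions a week loses 6 and leaves 18; two later weeks at three sessions restore 20. A hold in the final weeks could not be recovered in this way under a hard stop. If training instead runs until 24 sessions are done, as Study testing overview also suggests, a hold need cost no sessions.

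These figures describe the cost of the remedy. They do not measure the size of the defect.

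**The case against.** The strongest objection is that this is an article, and return to exercise after a serious event is the sort of operational detail left to fuller documents. The article points to a manual of operating procedures and to college policies. This stands as a limit: the text does not show that a re-approval step is absent from those documents. It does not dispose of the point, because the article chose to state a return rule, and the rule it states is not graded.

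A second objection is that the 48 h plan was meant for ordinary exertional complaints. It speaks of cooling down, which is no response to a heart attack, and serious events have their own emergency response elsewhere. That reading is plausible, and the immediate response is indeed graded. But the plan follows directly on a sentence naming all three classes, its trigger is not limited to non-serious events, and no other return condition is given.

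Third, the 48 h is a minimum and runs from the absence of symptoms. It permits a longer pause or a medical check. This is correct. A reader might infer that the protocol directs staff to restart a participant two days after a heart attack; the documents do not support that. They allow caution but do not require it.

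A reader might also extend the point to relapse during the study, since entry requires 30 relapse-free days. The article does not address relapse on study, but that is a separate omission and the return rule is not evidence for it.

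**Conclusion.** The point holds in limited form. The one return condition that the article states has no higher level for serious adverse events or clinical emergencies, and the only physician approval it requires is obtained before enrolment. The defect is in the wording of that rule. It does not show that the trial lacks a safeguard, since the manual or college policies may contain one.

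The size cannot be given as a number: the article states no rate of serious events, so neither the number of holds nor any effect on Go criterion 1 can be estimated. No estimate, error rate, sample size or Go/No Go calculation changes. The case for acting is participant safety at very small cost. With six of 15 participants enrolled on June 12, 2020, 15 − 6 = 9 were still to come, so a change then would have covered most of the sample. I would recommend the change, with medium confidence. The conclusion rests on reading adverse event in Table 1 in its ordinary sense, which includes serious ones.

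**What to change.** In the Scientific row of Table 1, limit the 48 h rule to non-serious adverse events and add: *After a serious adverse event or clinical emergency, the participant does no HIIT session and no maximal test until symptom-free for at least 48 h and until a physician has given renewed written approval covering both training and testing. The hold is recorded.* Leave the length of the hold to the physician. If the manual already contains such a step, a cross-reference is enough.

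The cost is one or two sentences, with no new staff or committee. The existing Physician's Approval form can serve if its wording covers training; the inclusion criterion mentions testing only, and the form is not shown, so it may need a line added. The process log lists no field for a safety hold, so one should be added, or the hold noted in the log books that already track missed sessions. The downside is that a held participant may miss sessions, some of which can be recovered through make-up sessions or a third weekly session.

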## Methods

### Recruitment

The study will recruit 15 pwMS-wd (i.e., a PDDS score of 3–6) from areas surrounding Berry College. Berry College is located in a highly accessible, rural area in the northwest of Georgia. We will recruit from areas between Atlanta, GA; Chattanooga, TN; and Birmingham, AL. Participants will be asked to provide their own transportation to Berry College. With regard to the sample population, this study focuses on the effects of HIIT in those with MS who are ambulatory, but report walking impairments, as this represents upwards of 75% of the MS community. Although the proposed range of participants (i.e., PDDS scores of 3–6) is wide, all participants within this range report at minimum gait impairment and at maximum are primarily wheelchair users but are able to walk 25 ft in under 2 min. Using this wide range will allow us to answer our key question, while maximizing our recruitment potential in a rural, likely underserved population. We will examine medication use, symptoms of spasticity, and depression in the study results.

Recruitment will occur through fliers provided to local and regional MS Society chapters, clinics, and doctor’s offices; flyers provided at local and regional MS Society events; advertisements on social media; email communication to the local and regional MS Society participants; and by word of mouth. This study will be described as an opportunity to participate in a study testing physiological and functional responses to exercise in persons with MS. Participants will be asked to contact the laboratory by telephone or email for further information about the study and screening for inclusion. See Fig. 1 for a diagram of participant movement from recruitment through completion of the program and Fig. 2 for the schedule of enrollment, intervention, and assessments.

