### Data analysis

All data will be entered, checked, and analyzed using SPSS Statistics (Chicago, IL). All data will initially be de-identified and checked for normality, outliers, errors, and missing entries. Process, resources, management, and scientific feasibility will be examined via descriptive statistics, percentage, and frequency analyses. The effect of the intervention will be determined using a repeated measures, 1-factor analysis of variance (Time) to identify significant changes over time. Multiple comparisons will be corrected using the Bonferroni correction. Disease type, medication use, symptoms of spasticity, and depression will be described and considered in the reporting of the study results. Overall effect sizes will be expressed as partial eta-squared, and small, medium, and large effects will be interpreted as values of 0.01, 0.06, and 0.14, respectively [49]. Feedback data will be reported via descriptive statistics, percentage, and frequency analysis.

We are defining clear Go/No Go Criteria for advancement to a RCT comparing RSTEP HIIT with MICE such that (1) 80% of participants (i.e., 12 participants) must complete at least 20 of the 24 prescribed sessions (i.e., 83%); this criterion is based on an expected dropout rate of ~ 15% [50]; (2) a clinically meaningful change in aerobic capacity and at least one additional outcome measure is required. Among those who successfully complete the trial (i.e., 83% of prescribed sessions), a half standard deviation improvement is necessary in aerobic fitness and at least one of the following outcomes: physical activity, walking, upper arm function, cognition, fatigue, or depression scores; this criterion is based on the universality of a half standard deviation threshold for detecting changes in health-related outcomes in chronic diseases [51, 52].

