The proposed study is not without limitations. The first relates to the absence of a control group. No control group will be used because we specifically aim to identify the feasibility and preliminary efficacy of the HIIT exercise protocol alone in pwMS-wd. Once the intervention has been deemed safe and scientifically efficacious through meeting the Go/No Go Criteria set forth in the proposed study design, future iterations of the study will include a control group engaging in MICE. Another limitation to the current study is that it is lab-based and requires that participants provide their own transportation. All efforts will be made to coordinate transportation with participants, including the use of para-transit services within the immediate area. Transportation will be included as a possible reason for declining participation in the study during recruitment. Finally, the inclusion/exclusion criteria limit the generalizability of the study to those who have MS, report walking dysfunction but are able to walk 25 ft, and are under the age of 65. Although the proposed range of participants (i.e., PDDS scores of 3–6) is wide, all participants within this range report at minimum gait impairment and at maximum are primarily wheelchair users but are able to walk 25 ft in under 2 min. Using this wide range will allow us to answer our key question, while maximizing our recruitment potential in a rural, likely underserved population.

As a new rehabilitative approach, HIIT has led to significant benefits in persons with MS who have mild disability, other clinical populations, and healthy populations [18, 19, 56, 60, 61]. HIIT presents a paradigm challenge for pwMS-wd, however, as this population seemingly should not engage in high-intensity exercise—our published pilot data challenge that paradigm as will the proposed research. The proposed research may create a shift among exercise rehabilitation programs for pwMS-wd that is synonymous with the exercise revolution that occurred in cardiac care [62] by demonstrating that a HIIT intervention is feasible and provides a significant stimulus to successfully condition severely deconditioned pwMS-wd. Future studies may generate data on the effects of HIIT in pwMS-wd on motor learning capacity and possible alterations to brain structure and integrity.

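### Table 1 and the Discussion promise a safety conclusion that descriptive event counts in 15 uncontrolled participants cannot support (minor, wording)

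*Protocol article*

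**What the plan says.** The sample is fixed under Recruitment: "The study will recruit 15 pwMS-wd (i.e., a PDDS score of 3–6) from areas surrounding Berry College". Under Feasibility metrics the design is uncontrolled: "Thus, a single treatment group, repeated measures study design is proposed".

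The Scientific row of Table 1 states how safety is assessed: "Adverse events, serious adverse events, and clinical emergencies will be reported and recorded". Its last column, on importance to phase II and III studies, states what that yields: "Establishes the safety and feasibility of the intervention and identifies considerations for alterations".

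Data analysis gives the method: "Process, resources, management, and scientific feasibility will be examined via descriptive statistics, percentage, and frequency analyses". The article names no tolerable event rate.

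The limitations paragraph of the Discussion returns to a safety conclusion: "Once the intervention has been deemed safe and scientifically efficacious through meeting the Go/No Go Criteria set forth in the proposed study design". It then describes a future trial with a comparator. The two Go/No Go criteria, set out under Data analysis, are an attendance threshold (12 of 15 participants completing at least 20 of 24 sessions) and an efficacy threshold: "a clinically meaningful change in aerobic capacity and at least one additional outcome measure is required".

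**The concern.** Two places in the article present safety as something this trial will settle. The evidence behind that is a tally of events in 15 people with no comparator. A sample of that size will often show no event of a given type even when the risk is large enough to matter, so a clean record is weak evidence. The limitations listed in the Discussion are the lack of a control group, travel to the laboratory, and the restricted population. None of them concerns how little 15 people can show about harm.

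What is at stake is how the result is carried forward. Table 1 offers it as input to later-phase studies of high-intensity exercise in people the Background calls severely deconditioned. The Risks section itself names death, heart attack and hospitalisation as possible consequences of maximal exercise. A later reader could cite this trial as having shown safety when it can only have given a first description.

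**Working it through.** **The plan's own figures.** The article gives no derivation of the sample size of 15 and no safety bound, so there is no safety figure to reproduce. Its related arithmetic is right: 0.80 × 15 = 12 participants, and 20/24 = 83.3% of sessions.

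**Inputs.** n = 15 (Recruitment); one group (Feasibility metrics); expected dropout about 15% (Data analysis). The 95% confidence level is my assumption, as the article states none for safety. The unit is the participant, and the risk is that of at least one event over the 12 weeks.

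**Step 1: upper limit with no events.** The exact binomial (Clopper-Pearson) limit for 0 of n is 1 − a^(1/n).
- One-sided 95%: 1 − 0.05^(1/15) = 0.181, or 18%.
- Two-sided 95%: 1 − 0.025^(1/15) = 0.218, or 22%.
- Check: (1 − 0.181)^15 = 0.05, as it should.

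**Step 2: chance of a clean record at a given true risk.** This is (1 − p)^15.

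| True 12-week risk | Chance that none of 15 is affected |
|---|---|
| 2% | 0.98^15 = 74% |
| 5% | 0.95^15 = 46% |
| 10% | 0.90^15 = 21% |

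**Step 3: if one participant is affected.** With 1 of 15, the exact upper limit is 27.9% one-sided and 31.9% two-sided.

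**Step 4: effect of dropout.** Having all 15 followed for 12 weeks is the best case. With 15% dropout, 15 × 0.85 = 12.75, about 13 people. If only those 13 gave full 12-week information, 0 of 13 would give 1 − 0.05^(1/13) = 20.6% one-sided and 24.7% two-sided.

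**Step 5: what exclusion would need.** The number of event-free participants needed to exclude risk p at one-sided 95% is ln(0.05)/ln(1 − p), rounded up: 29 for 10%, 59 for 5% and 299 for 1%.

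**Which events this applies to.** Protections against risk expects exhaustion, fatigue and muscle soreness. If those were counted, a record with no adverse event at all would be unlikely. The zero-event figures are therefore realistic mainly for serious adverse events.

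**The case against.** The strongest reply is that the point hangs on a verb in a relevance column. Other entries in that column use similar verbs loosely, for communication frequency or monetary cost, and the cell itself goes on to allow for alterations. The text introducing Table 1 is measured: safety will be examined, and the design aims at preliminary data. The next step is another trial, not clinical adoption. All of this stands, and it is why the point is minor. It does not remove the point, because the Discussion repeats a safety conclusion in running prose and nothing in the article qualifies it.

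Three stronger readings are tempting and are not supported.
- A reader might infer that the plan will treat few or no events as proof of safety. The article states no such rule. It says that events are recorded and described.
- A reader might call the absence of a confidence interval a defect in itself. Such an interval is commonly left to the analysis plan, which is not shown, and a descriptive analysis does not rule one out. The defect is the stated conclusion.
- A reader might fold in the fact that neither Go/No Go criterion counts adverse events. It does mean that meeting the criteria adds no direct evidence on event risk. Whether the Go rule should contain a safety element is a separate question, for the investigators.

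It could also be said that exposure is larger than 15, since 15 × 24 = 360 sessions are planned. No event in 360 sessions would give 1 − 0.05^(1/360) = 0.8% per session. That requires sessions within a person to be independent, which they are not, and it answers a different question from whether a participant is harmed over the programme.

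**Conclusion.** The concern holds as a point about wording. Fifteen participants in one group, summarised by counts, can provide preliminary safety data but cannot establish safety. With no serious adverse event among all 15, a per-participant 12-week risk of up to 18% (one-sided 95%; 22% as the two-sided 95% upper limit) would not be excluded, and a true 5% risk would go unseen 46% of the time. These figures assume independent participants, all 15 followed for the full period, and complete capture of events. Dropout would widen the limits. Severity is minor: the error lies in interpretation and affects neither the data collected nor how participants are handled.

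**What to change.** 1. In the Scientific row of Table 1, replace the claim that safety is established with: *Provides preliminary safety data*.
2. In the limitations paragraph of the Discussion, bring the statement that the intervention will have been judged safe into line with that wording.
3. Report the proportion of all enrolled participants with at least one adverse event, and separately with at least one serious adverse event, each with an exact (Clopper-Pearson) confidence limit whose sidedness is stated.
4. Add one sentence: with 0 of 15 affected, a risk of up to 18% (one-sided 95%) is not excluded.

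The cost is two wording changes, one added sentence and one exact limit per event class, with no new data. The safety statement becomes less favourable.
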